#### Analysis population

The primary analysis ITT population will include only vulnerable children.

#### Primary outcome analysis

The primary outcome (difference in M&MF scores between CUES and WL at 16 weeks) will be analysed within the vulnerable sub-population using a multilevel, mixed effects linear regression. Here, two random intercepts will be modelled — one at the school level to account for cluster randomisation, and one at the participant level to account for repeated outcome measurement over time. Time, baseline M&MF scores, participant sex, participant age, a dummy variable indicating treatment group, and the balancing variables used for randomisation will be included as fixed effect covariates. A treatment group by time interaction will also be included to allow for the treatment effect to differ at 8- and 16-week follow-ups.

Participants who do not contribute any outcome measurements of the primary outcome at either follow-up time point will not be included in the modified ITT population. Modelling assumptions will be checked and missing outcome data will be handled using maximum likelihood estimation. The framework of the trial is superiority.

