### Sample size {14}

In our feasibility trial [19], we found an effect size of 0.2. Assuming a type-1 error = 0.05 (two-sided test) with 90% power and an intraclass coefficient (ICC) of 0.025, a total of 68 schools are needed to be included in the analysis population, each with 25 vulnerable children. After accounting for a loss to follow-up at 5% of schools, and then a loss of 15% of vulnerable children, we will randomise 74 schools (1:1) to enrol 2220 vulnerable children.

In typical schools, there are approximately 75 Year 4 children, of which 40% are vulnerable, thus 30 vulnerable children per school. Approximately 5550 children will be enrolled in total, including 2220 vulnerable and 3330 non-vulnerable.

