## Discussion

The CUES for schools study will evaluate an interactive digital platform designed for teacher-facilitated delivery in primary school children. Trial procedures have been shown to be feasible, and in excess of 6000 children have received an expert-delivered version of the programme as part of local service delivery ([name] et al., personal communication).

This study will extend recruitment from inner London to outer London and the home counties. Feasibility study uptake was 11 of 36 eligible schools (30%) with 14 expressing interest. As we are recruiting across nearly 40 boroughs/counties, each with 40–80 eligible schools, we do not anticipate difficulty recruiting to our target of 74 schools and can increase this if insufficient numbers of vulnerable children are enrolled. No teacher declined participation. Our feasibility study employed a parental consent and child assent procedure: 8% of parents and 13% of children declined consent; just over 40% of parents and just over 75% of children returned a form and agreed participation. We anticipate higher parental return rates using an opt-out procedure. Parental and child requests to withdraw from delivery of the programme were low (*n* = 2), similar to in-service delivery, and child and teacher feedback in-service was consistent with acceptability, and safety, with no adverse events reported in the feasibility study, or during in-service delivery [5, 19]. Over 80% of children completing baseline assessments were retained in the feasibility study at follow-up.

Teachers varied in the timeliness of programme delivery in the feasibility study: we have implemented a weekly adherence check for this study to facilitate delivery within the 16-week window.

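### The primary model treats each school's effect as identical at 8 and 16 weeks; if school effects shift between visits, the 16-week standard error is somewhat too small

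*Protocol article*

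**What the plan says.** Primary outcome analysis in the Protocol article specifies a mixed linear model for the vulnerable children, with two random intercepts: "one at the school level to account for cluster randomisation, and one at the participant level to account for repeated outcome measurement over time". Among the fixed effects, "A treatment group by time interaction will also be included to allow for the treatment effect to differ at 8- and 16-week follow-ups". The primary contrast is the difference between arms at 16 weeks. The section also promises a check of model assumptions, without naming this one or saying what follows if it fails.

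The sample size section gives one ICC and no time point for it: "Assuming a type-1 error = 0.05 (two-sided test) with 90% power and an intraclass coefficient (ICC) of 0.025".

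Two other passages bear on whether schools may shift between visits. Plans for assessment and collection of outcomes {18a} has each class complete its measures together, and lets each visit fall up to two weeks early or four weeks late. The Discussion reports of the intervention: "Teachers varied in the timeliness of programme delivery in the feasibility study". The same sentence adds that a weekly adherence check has been introduced in response.

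**The concern.** The fixed part of the model lets the treatment effect differ by visit, but the random part does not let schools differ by visit. A school that sits above average at week 8 is assumed to sit equally far above it at week 16.

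The 16-week effect equals the effect averaged over both visits plus half the group-by-time interaction. The school intercept gives the averaged part its proper school-level variance. The interaction part is judged almost entirely against child-level residual variation. Any school-level change between visits is therefore missing from that part of the standard error.

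The error runs one way only, towards an interval that is too narrow, and it falls on the trial's single primary contrast. The expected standardised effect is small (0.2), so a borderline result is possible.

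**Working it through.** **The plan's own figure.** The inputs are in Sample size {14}: "In our feasibility trial [19], we found an effect size of 0.2"; two-sided 5%, 90% power and ICC 0.025; and "a total of 68 schools are needed to be included in the analysis population, each with 25 vulnerable children".

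- Per arm without clustering: 2 × (1.960 + 1.282)² / 0.2² = 526.
- Design effect: 1 + (25 − 1) × 0.025 = 1.6.
- 526 × 1.6 = 841.6 per arm; 841.6 / 25 = 33.7, rounded up to 34 schools per arm, or 68. This reproduces the stated figure.

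That calculation concerns a single time point, so the between-visit correlation does not enter it.

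**Set-up for the check.** Let r be the correlation of a school's effect between the two visits. The documents do not give it, so it is varied. Assumptions: total variance 1 and ICC 0.025 at each visit, 68 equal schools with 25 children each, no missing data and no covariates.

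- True variance of a school mean at 16 weeks: 0.025 + 0.975/25 = 0.025 + 0.039 = 0.064. The within-child correlation does not matter here, because the child-level part is 0.039 however it is split.
- School-by-visit variance: s = 0.025 × (1 − r).
- Part missed by the planned model: s/2.
- Part recovered through the pooled residual: between-school changes supply 66 of 66 + 68 × 24 = 1698 degrees of freedom, a share of 0.0389, so 0.0389 × s/2 comes back.
- Variance the fitted model reports: 0.064 − s/2 × (1 − 0.0389).

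At r = 0.5, s = 0.0125 and s/2 = 0.00625. The fitted variance is 0.064 − 0.00601 = 0.0580. The SE ratio is √(0.0580/0.064) = 0.952, and type I error is 2 × [1 − Φ(1.96 × 0.952)] = 6.2%.

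| r | model SE / true SE | type I error, asymptotic | type I error, simulated, t with 66 df |
|---|---|---|---|
| 1.0 | 1.000 | 5.0% | 4.9% |
| 0.9 | 0.991 | 5.2% | 5.1% |
| 0.8 | 0.981 | 5.5% | 5.4% |
| 0.7 | 0.971 | 5.7% | not run |
| 0.5 | 0.952 | 6.2% | 6.0% |
| 0 | 0.901 | 7.7% | 7.3% |

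The simulation used 100,000 balanced trials per setting. With a normal instead of a t reference, the rates were 5.4%, 5.5%, 5.8%, 6.5% and 7.8% at r = 1, 0.9, 0.8, 0.5 and 0. Since 5.4% appears even at r = 1, about 0.35 points of these come from the reference distribution and not from the omitted term. Adding a school-by-visit intercept gave 4.7% to 5.0% (t reference) at every r tried.

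If the ICC were 0.05, twice the planned value and purely an assumption, the asymptotic rates would be 5.7% at r = 0.8 and 6.9% at r = 0.5.

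**Could schools shift between visits?** The window lets the 8-week visit fall in weeks 6 to 12 and the 16-week visit in weeks 14 to 20. The gap between them can therefore run from 14 − 12 = 2 weeks to 20 − 6 = 14 weeks, depending on the school. Children assessed together also share the day and the setting. Both features apply to both arms and do not require CUES to work.

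**The case against.** The strongest counter-argument is that nothing in the documents shows any school-by-visit variance. If it is zero, the planned model is correct. That stands, and it is why the point must be conditional. A reader might infer that the type I error of this trial definitely exceeds 5%; the documents do not support that.

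A reader might also take the uneven delivery pace as evidence of inflation. It is weak evidence. Control schools receive CUES only after the 16-week visit, so pace varies in one arm only. If CUES did nothing in any school, pace could not create the variance. If CUES effects differed between schools around a zero average, only one arm would carry the extra variance. Halving the missed 0.00625 at r = 0.5 then gives √(1 − 0.0031/0.064) = 0.975 and a type I error of about 5.6%. The weekly adherence check should reduce it further. The shared classroom sitting and the visit window are the better argument, because they act in both arms.

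A third inference, that the trial is too small, also fails: the 68 schools follow from a single-time ICC.

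It is fair to say that a later SAP could refine the model, and that the check ignores the adjustment for baseline score, age, sex and the balancing variables, whose effect on r and on the residual ICC is unknown. But the random-effects structure is stated in the protocol, not left open, so this concerns a choice already made and not an omitted detail.

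**Conclusion.** The point holds conditionally. As written, the primary model imposes a correlation of exactly 1 between a school's effects at 8 and 16 weeks. If the true correlation is lower, the 16-week standard error is too small: by about 1% to 3% at correlations of 0.9 to 0.7 (type I error 5.2% to 5.7%), and by about 5% at 0.5 (6.2%). The asymptotic ceiling at ICC 0.025 is about 7.7%.

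These sizes rest on the assumed correlation, on the planned ICC applying at each visit, and on balanced, complete, unadjusted data. The importance is minor to moderate. The case for acting is that the error can only flatter the primary result and that removing it is cheap.

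**What to change.** Prespecify in the primary model a random intercept for each school at each follow-up visit, nested in school. Test the 16-week effect against a small-sample t reference. State in advance what happens if the new variance is estimated at zero or the model does not converge, for example reverting to the two-intercept model and reporting that this was done.

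An unstructured 2 × 2 school-level covariance over the two visits is a more general alternative, not the same model: it allows unequal school variances and a negative covariance, which the nested intercept does not.

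If the primary model is to stay as it is, the minimum is a prespecified sensitivity analysis that uses the 16-week scores only, or cluster-robust standard errors at school level.

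The cost is one model term and a sentence or two of text, with no change to data collection or sample size. The interval widens by about 1% (1/0.991) at correlation 0.9 and about 5% (1/0.952) at 0.5, and some fits will land on the zero-variance boundary.

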#### Secondary outcome analysis

Secondary outcome measures, like the primary outcome, will be analysed using mixed effects linear models in order to account for school-level cluster randomisation. However, as secondary outcomes are measured at one follow-up time period only, no participant-level random effect will be included within the model. Instead, time will be accounted for using fixed effects, with baseline outcome scores, participant sex, participant age, a dummy variable indicating treatment group, the balancing variables used for randomisation, and any additional baseline variables found to predict missingness in the primary outcome variable included as fixed effect covariates. Participants who do not contribute follow-up outcome data will be omitted from these analyses.

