### Intervention description {11a}

*CUES* comprises seven modules, with 24 lessons delivered over 12 weeks (within a 16-week window), in sessions of 20 min, two or three times/week. Schools will be asked to incorporate CUES into their social and emotional learning provision, so children do not have additional time in the classroom. The programme consists of digital interactive sessions. Teachers guide their class through the sessions using the content and interactivities that are part of the package. The package incorporates branding and characters designed to be appealing and engaging, in a mix of animation and video. Children in the intervention arm will receive CUES straight away. Children in the WL arm will receive CUES later in the term or in the following academic year.

For schools allocated to the CUES arm, teachers will watch the instructional video, and start the CUES programme. CUES delivery should start within 2 weeks of randomisation and proceed at an hour each week. There are 12 h of teaching to deliver within the 16-week window. Measures will be completed at baseline, T1 (8 weeks, primary outcome only) and T2 (16 weeks) in both arms.

The end of the trial will be defined as the last follow-up assessment at T2. WL participants will then receive CUES, at a time suitable in the context of the usual curriculum. This will not be part of the outcomes of the study and children will not be asked to complete any further measures.

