### Outcomes {12}

#### Primary outcome

We will use the M&MF [17] total score in vulnerable children at 16 weeks.

This measure comprises 16 items, each rated 0 (best) to 2 (worst), with total scores ranging from 0 to 32. The total score is made up from two subscales — emotional difficulties (M&MF-E, 10 items) and behavioural difficulties (M&MF-B, 6 items) — with children meeting the criterion for being vulnerable based on M&MF-E > 9 and/or M&MF-B > 5. The measure is designed specifically for use in schools to evaluate public health initiatives and has been widely used with children of this age group.

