#### Secondary outcomes

##### Vulnerable sub-population

M&MF-E 10-item subscale (M&MF items 1–10) at 16 weeks. Scores range from 0 to 20, with lower scores indicating more positive outcomes (clinical cut-off > 9).M&MF-B 6-item subscale (M&MF items 11–16) at 16 weeks. Scores range from 0 to 12, with lower scores indicating more positive outcomes (clinical cut-off > 5).Child Outcome Rating Scale (CORS) [18] 4-item total scale at 16 weeks. This scale is designed to measure wellbeing and distress, with each item rated 0 (worst) to 10 (best) with scores below 32 considered to represent clinical levels of distress/poor wellbeing.Child workbook 7-item wellbeing rating scores at 16 weeks. Each item is rated from 0 (worst) to 10 (best), with total scores ranging from 0 to 70.Child workbook 8-item cognitive rating scores at 16 weeks. Each item is rated from 0 to 1, with one item rated from 0 to 2. Total scores range from 0 to 9.

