Data completeness was good (primary outcome missing for 2% of children at baseline, < 1% at follow-up; 0–11% missing data for single items on secondary outcomes, mode = 0), indicating children found the assessments acceptable. Completing all measures at three time points elicited informal feedback of fatigue at repetition. In response, we now ask for only the primary outcome at T1 (8 weeks). Measures are self-report by children and teachers. While standardised measures are designed and well-validated for school use with this age group, there is potential for bias as neither children nor teachers can be blinded to allocation. Thus, the self-report nature of the assessments may offer a limitation. Previous authors have argued that the waiting list control may artificially inflate the between-group difference [24]. It should be noted the same effect was seen in the clinical service evaluation as within the feasibility study point estimate, which may not support this. The same teachers that delivered the CUES for schools lessons to the children carried out the teacher-rated assessments — so this outcome may suffer assessor-rated bias.

The programme is designed to improve emotional/behavioural problems specifically for vulnerable children participating within whole class groups. Service data has shown small, yet consistent improvements, which were replicated in feasibility data. Given the mixed outcome data for vulnerable children taking part in similar programmes in schools to date [9, 10], reliably improving their outcomes is a key public health priority. A significant strength is that the programme can be delivered by teachers without extensive additional training. The training provided is integral to the platform except for a short instructional video on presentation style. Implementability should therefore be high, addressing concerns about the continued rollout of research-based initiatives [13].

While the platform content is set, teachers are free to adapt their own delivery to accommodate local variations in context and cultural needs. The recruitment areas are socio-economically diverse, and the programme is designed to be suitable for all schools irrespective of size or setting.

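### The single-follow-up premise of the secondary-outcome model is untrue for M&MF-E and M&MF-B, which are also observed at 8 weeks; the loss is modest but avoidable

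*Protocol article*

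**What the plan says.** All places are in the protocol article.

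- **Secondary outcome analysis** specifies a mixed linear model with a school effect. It gives one reason for leaving out the participant effect: "as secondary outcomes are measured at one follow-up time period only, no participant-level random effect will be included within the model". It continues: "Instead, time will be accounted for using fixed effects". Baseline score is a covariate, baseline predictors of missingness in the primary outcome are added, and children without follow-up data are left out.
- **Primary outcome** says of the M&MF: "The total score is made up from two subscales", namely M&MF-E (10 items) and M&MF-B (6 items).
- **Secondary outcomes** for the vulnerable sub-population include "M&MF-E 10-item subscale (M&MF items 1–10) at 16 weeks" and "M&MF-B 6-item subscale (M&MF items 11–16) at 16 weeks". Both also appear in the whole-school list.
- **Intervention description {11a}** gives the schedule: "Measures will be completed at baseline, T1 (8 weeks, primary outcome only) and T2 (16 weeks) in both arms". Table 1, the data collection section and the Discussion agree.
- **Primary outcome analysis** uses both follow-ups, with a school random intercept and "one at the participant level to account for repeated outcome measurement over time", plus a treatment-by-time interaction. A child is excluded only if both follow-ups are missing, and missing outcomes are handled by maximum likelihood.

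**The concern.** The whole 16-item M&MF is collected at week 8, so both subscale scores exist at week 8 as well as week 16. The reason given for using a simpler model on secondary outcomes therefore fails for these two.

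Three things follow if the text is applied as written:

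- Week-8 subscale data are collected and then not used in the subscale comparisons. The whole-school list has no M&MF total, so the week-8 M&MF data of the roughly 3330 non-vulnerable children would enter no listed treatment comparison.
- A child seen at week 8 but not at week 16 contributes to the M&MF total but to neither of its components.
- The primary analysis lets the week-8 score inform a missing week-16 score. The subscale analyses rely on baseline variables only.

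The sentence on time adds an ambiguity, because it describes a term that a one-follow-up model cannot use.

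**Working it through.** **1. Is the premise true for each outcome?** (Table 1, Intervention description, outcome lists)

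| Outcome | Week 8 | Week 16 | One follow-up only? |
|---|---|---|---|
| M&MF total (primary) | yes | yes | no, and both are modelled |
| M&MF-E, M&MF-B (secondary) | yes, as items of the M&MF | yes | no |
| CORS, workbook, teacher outcomes | no | yes | yes |

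**2. Which children are analysed?** With week-8 data only, a child is in the primary analysis (at least one follow-up) and out of the subscale analyses (no outcome at the single follow-up modelled).

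**3. The plan's own sample size.** The point does not rest on it, but its inputs are used below.
- Per arm without clustering: 2 × (1.960 + 1.282)² / 0.2² = 525.4.
- Design effect: 1 + (25 − 1) × 0.025 = 1.6.
- Schools per arm: 525.4 × 1.6 / 25 = 33.6, so 34, and 68 in total, as stated.
- Inflation: 68 / 0.95 = 71.6, so 72 (74 stated). 25 / 0.85 = 29.4, about 30. 74 × 30 = 2220, as stated.

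None of this changes with the fix.

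**4. How many children could be affected?** The protocol gives a 15% loss of vulnerable children but not how many of them would have week-8 data. Take the 15% as missing week 16 and 74 × 0.95 = 70.3, about 70 retained schools. Then 30 × 0.15 = 4.5 vulnerable children per school miss week 16.

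| Assumed share of these with week-8 data | Vulnerable children (of 70 × 30 = 2100) | Whole population (of 70 × 75 = 5250, same 15% loss assumed) |
|---|---|---|
| 0% | 0 | 0 |
| 25% | 79 | 197 |
| 50% | 157 | 394 |
| 100% | 315 | 788 |

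**5. How much precision is at stake?** Assume a fraction f = 0.05 to 0.10 with week-8 data only, a correlation between follow-ups of 0.5 to 0.7, a correlation of 0.5 between baseline and each follow-up, and the protocol's ICC of 0.025 for the subscales too.
- The model adjusts for baseline, so the partial correlation applies: (ρ − 0.5²) / (1 − 0.5²). This gives 0.33 for ρ = 0.5 and 0.60 for ρ = 0.7.
- Gain before clustering, approximately f × r² / 0.85: 0.05 × 0.33² / 0.85 = 0.65%, and 0.10 × 0.60² / 0.85 = 4.2%.
- Only the within-school part of the variance of a school mean benefits: (0.975 / 25) / (0.025 + 0.975 / 25) = 0.039 / 0.064 = 0.61.
- Gain in effective sample: 0.65% × 0.61 = 0.4%, up to 4.2% × 0.61 = 2.6%.

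As a cross-check over a wider range, take n1 = 0.85 with week 16, n2 with week 8 only, and a within-school variance ratio v = 1 − r² × n2 / (n1 + n2). The variance of a school mean is 0.025 + (0.975 / 25.5) × v, against the same expression with v = 1.
- r = 0.4, n2 = 0.15 × 0.25 = 0.0375: v = 0.993, and the standard error is multiplied by 0.998.
- r = 0.8, n2 = 0.15: v = 0.904, and the standard error is multiplied by 0.971.

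The standard error therefore falls by about 0.2% to 3%. The upper end requires every child who misses week 16 to have been seen at week 8.

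**6. The time term.** With week-16 records only, time is constant and cannot be estimated. If both follow-ups were entered for the subscales, time would have a role, but two records from one child would be treated as independent given school, so the standard errors would rest on a wrong covariance. The school effect may absorb part of this, and I have not quantified it. Since no treatment-by-time term is listed, the coefficient would also average the 8- and 16-week effects instead of giving the 16-week effect. Neither reading suits the subscales.

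**The case against.** The strongest defence is that the subscales are defined at 16 weeks. A week-16 model with baseline as a covariate and a school effect is a valid way to estimate that contrast, and the methods are introduced as brief, with a SAP to follow. The validity of the week-16 model stands. But the primary outcome is also defined at 16 weeks and is still modelled with both follow-ups. The article does not leave the subscale model open; it gives a reason for departing from the primary model, and that reason is untrue for the subscales.

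The secondary model also adds baseline predictors of missingness, which supports a missing-at-random assumption given baseline. This stands and reduces the concern. It does not supply what the week-8 score would add, namely information on how the child was doing after randomisation.

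The precision gain is small, and that stands too. A figure of 1.5–6% might be inferred from the unadjusted correlations (0.05 × 0.5² / 0.85 = 1.5%; 0.10 × 0.7² / 0.85 = 5.8%), but it ignores both baseline adjustment and clustering.

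Two stronger readings are tempting:

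- **That the time sentence would halve the estimated effect.** This needs baseline records stacked as outcomes with no treatment-by-time term, so that a near-zero baseline difference is averaged with the week-16 difference. The protocol does not describe that model. It makes baseline score a covariate and speaks of one follow-up.
- **That the subscale effects ought to sum to the effect on the total, and would after correction.** The protocol does not say so. Even under the primary model structure, each score would be adjusted for its own baseline with its own variance components, so exact additivity would not follow.

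**Conclusion.** The point holds as a factual mismatch with a modest consequence. The stated justification is wrong for M&MF-E and M&MF-B in both populations. As written, it leaves the 8-week subscale data unused and removes children whom the primary analysis keeps.

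The case for correcting it is mainly coherence: the total and its components should rest on the same children and the same missing-data assumption. The precision at stake is about 0.4–2.6% of effective sample under the assumptions in step 5, and at most about 3% of the standard error under the wider ones. The number of children with week-8 data only is not in the document. It could be close to zero, or as high as about 315 vulnerable children if the 15% loss applies to week 16 alone.

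Confidence is high in the mismatch and limited in the size. The effect is confined to secondary outcomes, and nothing here supports a claim of a biased or halved treatment effect.

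**What to change.** In the SAP, and in the protocol if it is amended:

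- Analyse M&MF-E and M&MF-B, in both the vulnerable and the whole-school populations, with the primary model structure: school and participant random intercepts, 8- and 16-week outcomes, and treatment-by-time, reporting the 16-week contrast.
- Apply the primary analysis's inclusion rule to these outcomes, so that a child with either follow-up is kept.
- Restrict the single-follow-up model to the CORS, workbook and teacher outcomes, and delete time from it.

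The cost is a few sentences. The data are already scheduled for collection and the sample size is unaffected. The change should be made before the SAP is signed off and the database is locked.

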### Methods in analysis to handle protocol non-adherence and any statistical methods to handle missing data {20c}

Data will be explored for structural missingness and reported accordingly. The primary population under investigation will be the modified intention to treat (ITT). The ITT population will be defined as all children with at least one post baseline timepoint.

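### Baseline predictors of missing M&MF are added to the secondary models but left out of the primary M&MF model, with no reason given

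*Protocol article*

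**What the plan says.** Protocol article, Primary outcome analysis, on the fixed effects: "Time, baseline M&MF scores, participant sex, participant age, a dummy variable indicating treatment group, and the balancing variables used for randomisation will be included". A treatment-by-time interaction and random intercepts for school and child complete the model. On missing data, the same section says "missing outcome data will be handled using maximum likelihood estimation". It also restricts who is analysed: "Participants who do not contribute any outcome measurements of the primary outcome at either follow-up time point will not be included".

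Secondary outcome analysis gives nearly the same covariates and then extends them with "any additional baseline variables found to predict missingness in the primary outcome variable included as fixed effect covariates". These models treat each outcome as having a single follow-up and leave out children without it.

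The section on missing data ({20c}) adds only "Data will be explored for structural missingness and reported accordingly" and the definition of the modified ITT population. It does not carry the predictors into the primary model.

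Under Outcomes {12}, the M&MF total is the sum of the 10-item emotional and 6-item behavioural subscales. Both subscales are secondary outcomes in the vulnerable children at 16 weeks.

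**The concern.** Likelihood estimation from a mixed model is valid when outcomes are missing at random given what the model contains. A baseline variable that drives both missingness and outcome, and is left out, can break that condition. Children with neither follow-up score are excluded, so for them the 8-week score offers nothing and baseline covariates are the only adjustment available.

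The plan will search for variables that predict missing M&MF, and then use them in the models for every outcome except the M&MF total. At stake is the primary 16-week contrast, and also its coherence with the two subscale results that readers will set beside it.

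The secondary rule has a narrower weakness. It applies predictors of a child's missing M&MF to the teacher ratings of class behaviour and coping, where missingness arises with the teacher.

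**Working it through.** **The plan's own figure.** Inputs from Sample size {14}: "Assuming a type-1 error = 0.05 (two-sided test) with 90% power and an intraclass coefficient (ICC) of 0.025"; "we found an effect size of 0.2"; "a total of 68 schools are needed to be included in the analysis population, each with 25 vulnerable children".

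- Per arm without clustering: 2 × ((1.960 + 1.282)/0.2)² = 525.4, so 526.
- Design effect: 1 + (25 − 1) × 0.025 = 1.6. Then 526 × 1.6 = 841.6 per arm, and 841.6/25 = 33.7, so 34 schools per arm, or 68. This reproduces the plan. Power with 34 × 25 = 850 per arm is 0.903.
- Losses: 68/0.95 = 71.6, so 72 schools (74 stated); 25/0.85 = 29.4, so 30 children; 74 × 30 = 2220.
- Standard error implied by the design: √(2 × 1.6/850) = 0.061 SD.

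The sample size is not in question. It supplies the scale for what follows.

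**The two covariate lists.**

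| Term | Primary | Secondary |
|---|---|---|
| Baseline score of the outcome, sex, age, treatment, balancing variables | yes | yes |
| 8-week score used | yes, by likelihood | no |
| Baseline predictors of missing M&MF | no | yes |

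**Possible size.** The protocol gives no figures for this, so every input here is an assumption. The simulation has 1,000,000 children and no clustering. True effects are −0.1 at 8 weeks and −0.2 at 16 weeks, and the outcome SD is close to 1. In each arm 15% are missing at 16 weeks, and half of those are also missing at 8 weeks. One baseline variable X, not in the model, predicts missingness. The estimates are maximum likelihood using both follow-ups. Missingness slopes are log-odds per SD of X.

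| Slope of outcome on X | Missingness slope, control / CUES | Estimate without X | Estimate with X | Distance from −0.20 without X |
|---|---|---|---|---|
| 0.1 | 0.5 / 0.5 | −0.1986 | −0.1986 | 0.0014 |
| 0.1 | 0 / 0.5 | −0.2039 | −0.1981 | 0.0039 |
| 0.1 | 0 / 1.0 | −0.2103 | −0.1998 | 0.0103 |
| 0.1 | −0.5 / 0.5 | −0.2116 | −0.2004 | 0.0116 |
| 0.3 | 0.5 / 0.5 | −0.1971 | −0.1976 | 0.0029 |
| 0.3 | 0 / 0.5 | −0.2182 | −0.2005 | 0.0182 |
| 0.3 | 0 / 1.0 | −0.2281 | −0.1992 | 0.0281 |
| 0.3 | −0.5 / 0.5 | −0.2345 | −0.2016 | 0.0345 |

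In the two rows with equal mechanisms, the estimates with and without X agree closely, so the small distance from −0.20 is simulation noise. Where the mechanism differs by arm, the bias is about 0.004 to 0.035 SD. That is 0.0039/0.2 = 2% to 0.0345/0.2 = 17% of the planned effect, and at most 0.0345/0.061 = 0.57 of a standard error. With X in the model the estimate returns to about −0.20.

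A cruder check lets the loss rate differ instead. With 20% lost in one arm and 10% in the other, and missing children 0.3 SD worse through X (all assumed), the bias is (0.20 − 0.10) × 0.3 = 0.03 SD, or 15% of 0.2. This formula gives no credit for the 8-week scores.

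**The case against.** The strongest defence is that the two kinds of model differ for a reason. The secondary models are complete-case with one follow-up, so baseline covariates are their only route to a plausible missing-at-random assumption. The primary model keeps a child who was seen at 8 weeks and missed at 16. It also conditions on baseline M&MF, sex, age, and school deprivation and size (the balancing variables), with a school intercept. Fixing the primary covariates in advance is a legitimate choice, and the text is a summary ahead of a SAP. Much of this stands, and it limits the size of the problem. However, the protocol does not give that reason, and it does not help children with neither follow-up. The protocol also states both lists, so a SAP that followed them would keep the mismatch.

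Three stronger readings are tempting, and the document does not support them:

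- **That the plan regards this adjustment as necessary and then withholds it from the primary analysis.** It prescribes the adjustment for the secondary models and never calls it necessary.
- **That the primary contrast is biased as planned.** A variable that predicts both dropout and M&MF is not sufficient. Missingness must also differ by arm.
- **That all secondary outcomes go missing for their own reasons.** Child measures are completed together in class (Plans for assessment and collection of outcomes {18a}), so absence from the session probably drives most missingness across them. Predictors of missing M&MF are then a reasonable common choice. The objection is fair only for the teacher ratings.

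**Conclusion.** The mismatch is in the text and is unexplained: the two subscales are adjusted for predictors of missing M&MF, and their total is not. The primary model is partly protected, so the consequence is conditional. The 16-week contrast may be biased if an omitted baseline variable predicts both missingness and M&MF, and missingness differs by arm.

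Under the assumed inputs the bias is about 0 to 0.035 SD against the planned 0.2, and about zero when the mechanism is the same in both arms. The range illustrates size and is not a bound. The bias could also run in the opposite direction if the arms' roles were exchanged.

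A difference by arm is plausible here. Children, teachers and the researchers supporting assessment are unblinded, the control is a waitlist, the plan allows for 15% loss of vulnerable children, and it lists no retention measures. The point merits a correction but does not undermine the design.

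**What to change.** In Primary outcome analysis, state that baseline variables found to predict missing M&MF, identified before lock and blind to arm, enter the primary model as fixed effects. If a fixed primary covariate set is preferred, say so, and put these variables in a pre-specified sensitivity version of the same model. For the teacher-rated outcomes, use predictors of those outcomes' own missingness.

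The candidate variables are already collected at baseline, the sample size does not change, and a few more fixed effects are easily carried by 68 × 25 = 1,700 analysed children. The costs are:

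- Some covariate selection depends on the data, so the selection rule should be fixed in the SAP.
- The protocol places all analyses after lock, so the SAP should say that this blinded step comes earlier.
- A search on data pooled over arms could miss a variable that acts in opposite directions in the two arms, which is the setting that gave the largest bias above. The fix reduces the risk but does not remove it.
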